|--|----------------------------------------------------------------------------------------------------------------------------------------------------------------------------------------------------------------------------------------------------------------------------------------------------------------------------------------------------------------------------------------------------------------------------------------------------------------------------------------------------------------------------------------------------------------------------------------------------------------------------------------------------------------------------------------------------------------------------------------------------------------------------------------------------------------------------------------------------------------------------------------------------------------------------------------------------------------------------------------------------------------------------------------------------------------------------------------------------------------------------------------------------------------------------------------------------------------------------------------------------------------------------------------------------------------------------------------------------------------------------------------------------------------------------------------------------------------------------------------------------------------------------------------------------------------------------------------------------------------------------------------------------------------------------------------------------------------------------------------------------------------------------------------------------------------------------------------------------------------------------------------------------------------------------------------------------------------------------------------------------------------------------------------------------------------------------------------------------------------------------------------------------------------------------------------------------------------------------------------------------------------------------------------------------------------------------------------------|

|                                                    |                                                                                                                                                                                                                                                                                                                                                                                                                                                                                                                                                                                                                                                                                                                                                                                                                                                                                                                                                                                                                                                                                                                                                                                                                                                                                                                                                                                                                                                                          |
|----------------------------------------------------|--------------------------------------------------------------------------------------------------------------------------------------------------------------------------------------------------------------------------------------------------------------------------------------------------------------------------------------------------------------------------------------------------------------------------------------------------------------------------------------------------------------------------------------------------------------------------------------------------------------------------------------------------------------------------------------------------------------------------------------------------------------------------------------------------------------------------------------------------------------------------------------------------------------------------------------------------------------------------------------------------------------------------------------------------------------------------------------------------------------------------------------------------------------------------------------------------------------------------------------------------------------------------------------------------------------------------------------------------------------------------------------------------------------------------------------------------------------------------|
| TOLERABILITY / SAFETY
ENDPOINTS                 | 
 
Cumulative incidence of serious adverse events
 
Discontinuation or temporary suspension of therapy
 
Changes in white cell count, hemoglobin, platelets, creatinine, glucose, total bilirubin, alanine aminotransferase (ALT), aspartate aminotransferase (AST), uric acid over time
 
Occurrence of drug induced liver injury (DILI) in various treatment arms
 
Sub-study A: bleeding events
 
                                                                                                                                                                                                                                                                                                                                                                                                                                                                                                                                                                                                                                                                                                                                                                                                                                                                                                                                                                                            |
| PHARMACOKINETIC /
PHARMACODYNAMIC
ENDPOINTS  | 
Within all patients randomized to Lopinavir/Ritonavir treatment a drug-drug interaction check will be performed in a retrospective manner. However, if questions concerning CYP interactions or QTc prolonging agents occur during the trial, a drug-drug-interaction check will be possible after contact with the Department of Clinical Pharmacology.
 
 
Pharmacokinetics of antiviral treatment (if assays are available, e.g. lopinavir/ritonavir)
 
                                                                                                                                                                                                                                                                                                                                                                                                                                                                                                                                                                                                                                                                                                                                                                                                                                                                                                                                                            |
| QUALITY OF LIFE /
PHARMACOECONOMIC
ENDPOINTS | Substudy B, as specified above.                                                                                                                                                                                                                                                                                                                                                                                                                                                                                                                                                                                                                                                                                                                                                                                                                                                                                                                                                                                                                                                                                                                                                                                                                                                                                                                                                                                                                                          |
| STATISTICAL METHODOLOGY                            | 
Primary Endpoint
 
Time to sustained improvement (i.e. >48h) of one category from admission in the 7-point clinical performance scale, which will be measured daily till day 29
 
Null and alternative hypotheses:
 
H0 There is not difference between the treatment arms with regards to the primary endpoint
 
H1: There is a significant difference between treatment arms with regards to the primary efficacy endpoint
 
Sample size calculation
 
As the initial phase of the main study will start with not all treatment arms, the initial sample size calculation is based on the comparison of two treatment arms. A sample size of 100 per treatment arm will ensure a power of >80% to detect an improvement of 6 days in the primary endpoint time to clinical improvement, if the median time in one group is 16 days.
 
Based on the recent publication of Cao et al. (1) we assumed that the median time in the treatment arm 2 (Lopinavir/Ritonavir) is about 16 days. Assuming an improvement between either two groups of 6 days in the median time to clinical improvement, a log-rank test at a two-sided significance level of <math>\alpha = 0.05</math> with a sample size of 100 per treatment group would yield a power larger >80%. These assumptions would translate in a hazard ratio of 1.6 when assuming exponential time-to-event curves.
 |

|  |                                                                                                                                                                                                                                                                                                                                                                                                                                                                                                                                                                                                                                                                                                                                                                                                                                                                                                                                                                                                                                                                                                                                                                                                                                                                                                                                                                                               |
|--|-----------------------------------------------------------------------------------------------------------------------------------------------------------------------------------------------------------------------------------------------------------------------------------------------------------------------------------------------------------------------------------------------------------------------------------------------------------------------------------------------------------------------------------------------------------------------------------------------------------------------------------------------------------------------------------------------------------------------------------------------------------------------------------------------------------------------------------------------------------------------------------------------------------------------------------------------------------------------------------------------------------------------------------------------------------------------------------------------------------------------------------------------------------------------------------------------------------------------------------------------------------------------------------------------------------------------------------------------------------------------------------------------|
|  | 
There is currently only limited or no data available on expectable effect sizes. Therefore, we plan an interim analysis as soon as 20 and 50 patients have been randomized to the respective treatment arms. Study arms may be closed at interim analyses and after the second interim analysis, a sample size recalculation will be performed.
 
In short, n=100 per group for the asunercept (in total 400 patients) will be included. For the Pentaglobin part, n=20 will be included.
 
Statistical methodology
 
To test whether there is a difference between treatment arms, a log rank test will be performed at two-sided level alpha of 5%. The time-to-event data will be visualized by Kaplan-Meier plots.
 
Interim analysis
 
After inclusion of 20 and 50 patients per treatment arm.
 
The first interim analysis is mainly for safety and futility only. In the second interim analysis a sample size reassessment will be performed. To allow for early stopping in case overwhelming effects are observed, an alpha spending function with O'Brien and Fleming (OF) boundaries will be used.
 
For all sub-studies detailed statistical analysis plans will be created, which will also provide detailed information on sample size calculation.
 
Treatment arm four will only be analyzed in a descriptive manner.
 |
|--|-----------------------------------------------------------------------------------------------------------------------------------------------------------------------------------------------------------------------------------------------------------------------------------------------------------------------------------------------------------------------------------------------------------------------------------------------------------------------------------------------------------------------------------------------------------------------------------------------------------------------------------------------------------------------------------------------------------------------------------------------------------------------------------------------------------------------------------------------------------------------------------------------------------------------------------------------------------------------------------------------------------------------------------------------------------------------------------------------------------------------------------------------------------------------------------------------------------------------------------------------------------------------------------------------------------------------------------------------------------------------------------------------|

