| OBJECTIVES | 
Primary Objective
 
 
To investigate the efficacy of various experimental therapeutics for patients with severe acute respiratory syndrome coronavirus 2 (SARS-CoV-2); for efficacy assessment a 7 category ordinal scale for clinical severity assessment as proposed by the World Health Organization will be used: 
 
Time to sustained improvement of one category from admission
 
 
 
 
Secondary Objectives
 
 
To assess efficacy according to the National Early Warning Score (NEWS): 
 
Time to discharge or to a NEWS of <math>\leq 2</math> and maintained for 24 hours, whichever occurs first
 
Change from baseline (once daily)
 
 
 
Oxygenation 
 
Oxygenation free days until day 29
 
Incidence and duration of new oxygen use during the trial
 
 
 
Mechanical Ventilation 
 
Ventilator free days until day 29
 
Incidence and duration of new mechanical ventilation use during the trial
 
 
 
Viral load/viral clearance 
 
Baseline, then three times a week
 
 
 
Hospitalization 
 
Duration of hospitalization
 
Duration of intensive care unit treatment
 
Intensive care unit admissions
 
 
 
Mortality 
 
15-day, 29-day, 60-day, 90-day mortality
 
 
 
Sub-Study A: number of thromboembolic events
 
Renin-Angiotensin System (RAS)- and bradykinin fingerprint at baseline and at least once weekly (on days 7<math>\pm</math>1, 14<math>\pm</math>1, 21<math>\pm</math>1, 28<math>\pm</math>1, through recovery), depending on whether patients are hospitalized with SARS-CoV-2 infection, or treated as outpatients (the latter applies only to patients in sub-study B). RAS- and bradykinin
 
 |

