## 8.5 Study procedures

### 8.5.1 General rules for trial procedures

- All study measures like blood sampling and measurements (vital parameters, ECG, etc.) have to be documented with date (dd:mm:yyyy).
- In case several study procedures are scheduled at the same time point, adverse events will be collected first and study medication will be administered after.
- The dates of all procedures should be according to the protocol. The time margins mentioned in the study flow chart are admissible. If for any reason, a study procedure is not performed within scheduled margins a protocol deviation should be noted, and the procedure should be performed as soon as possible or as adequate.
- If it is necessary for organizational reasons, it is admissible to perform procedures which are scheduled for one visit at two different time points. Allowed time margins should thereby not be exceeded.

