### 8.5.3 Treatment phase (First Day of Treatment = Day 1)

For treatment arms 2 the minimum duration of treatment is seven days but at least until sustained improvement. For treatment arm 3 (remdesivir) treatment duration is 5-10 days. In case of an early discharge from hospital (before 7 days) patients will receive the required treatment to take it at home (treatment arms 2). In case of an early discharge patients will be called (by telephone) on day 11 and 29 to obtain information on the clinical endpoints.

For all patients the clinical endpoints (including WHO ordinal scale, NEW Score, oxygenation, etc.) will be obtained on a daily basis.

Blood pressure, heart rate, respiratory rate, oxygen demand, oxygen saturation, mode of oxygen delivery, concomitant medication is documented as part of routine care. Laboratory analyses (similar to screening investigation, without HBsAg, but with D-Dimer and anti-FXa activity and troponin levels only between day 5 and 11) will be performed three times a week, and in case of clinical necessity possibly more often.

Blood sampling is recommended three times a week, if possible (e.g. Mo, Wed, Fr), to monitor patients for medical reasons. If this is not feasible because it is against hospital rules or puts too much burden on the already stressed health care workers, the frequency of blood sampling can be reduced without being a protocol deviation.

If such assays are available, pharmacokinetic measurements of antiviral substances will be performed (e.g. trough level analysis for lopinavir/ritonavir after 24h and on day 4 to 7).

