#### 8.5.4 End-of-study (EOS) examination

For all patients except for sub-study B and, in part, C the study will end on study day 29, although also day 60 and 90 mortality will be assessed. Either a telephone call or, if the patients are still hospitalized, an EOS visit will be performed. Given the specific circumstances, a formal visit at a hospital will not be required for each patient and only be performed for specific circumstances (e.g. ongoing, relevant side effects). Otherwise the telephone call will be the EOS. For sub-study B or C the study will end with patient death or full recovery. In case a telephone call is the EOS, females with childbearing potential will be asked about possible pregnancies, asked to do a pregnancy test or asked about the date of their last menstruation.

For control groups the last blood sample/oral/nasopharyngeal swab will be the EOS.

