## 11.5 Missing, unused and spurious data

Missing data will not be imputed.

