## 11.6 Endpoints analysis

### 11.6.1 Primary endpoint analysis

All primary analyses will be on the modified ITT set and the analysis based on the per protocol set will be provided as supportive analysis.

The primary endpoint is time to clinical improvement which is defined as time from randomization to an (sustained) improvement of at least one category on two consecutive days compared to the status at randomization measured on a seven-category ordinal scale (proposed by WHO).

The 7-categories of the World Health Organization proposed scale, as follows:

1. Not hospitalized, no limitations on activities
2. Not hospitalized, limitation on activities;
3. Hospitalized, not requiring supplemental oxygen;
4. Hospitalized, requiring supplemental oxygen;
5. Hospitalized, on non-invasive ventilation or high flow oxygen devices;
6. Hospitalized, on invasive mechanical ventilation or ECMO;
7. Death.

During hospitalization this score will be determined daily (till day 29). If a patient is released from the hospital before day 29, the score will be determined at day 11 and 29 (and day 60 in clazakizumab arm) after randomization (depending when the patient was released or by telephone call).

The time to clinical improvement will be visualized by Kaplan-Meier Plots. The comparisons of the time-to-event curves will be performed using a log-rank at a two-sided level alpha of 5%.

(Please note in the initial phase only treatment arms (1-3, 5) might be available for the platform trial. A closed test procedure will be implemented to control the multiple level alpha. More details will be provided in the statistical analysis plan.

Additionally, a Cox-proportional hazard model will be performed. In this model we will use treatment as factor and it will be adjusted for calendar time to account for time trends (e.g. severity of cases might change over time).

Furthermore, we will include sex and age as factors in the model.

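### Table 1 lets the final contact in arms 1-4 fall up to seven days before day 29, so for discharged patients the end of the oxygen- and ventilator-free count may never be collected

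*Protocol*

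**What the plan says.** - **Endpoints.** The synopsis, section 6.2 and section 11.6.2 list "Oxygenation free days until day 29" and "Ventilator free days until day 29". Section 11.6.2 analyses both as continuous counts by ANCOVA and calls all secondary analyses exploratory.
- **Schedule.** Table 1 places the follow-up call or visit for treatment arms 1-4 at day 29, plus or minus seven days. Section 8.5.1 adds: "The time margins mentioned in the study flow chart are admissible".
- **Text.** Section 8.5.3 says: "In case of an early discharge patients will be called (by telephone) on day 11 and 29 to obtain information on the clinical endpoints". Section 11.6.1 says: "If a patient is released from the hospital before day 29, the score will be determined at day 11 and 29". Section 7.1.5 evaluates every patient's clinical status on day 29. None of these gives a margin.
- **Inpatients.** Section 11.6.1: "During hospitalization this score will be determined daily (till day 29").
- **Closing contact.** Section 8.5.4 ends the main study on day 29 and requires a formal hospital visit only in special circumstances. "Otherwise the telephone call will be the EOS". After that only mortality at days 60 and 90 is planned. Section 10.1 adds check-ups where disease or side effects are still ongoing.
- **Missing data.** Section 11.5: "Missing data will not be imputed".

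**The concern.** A margin after day 29 does no harm, because a later call can ask about the period up to day 29. A margin before day 29 is different: a call on day 22 cannot report an event on day 25. For a patient at home it is also the last planned contact that would collect oxygen use, ventilation, readmission or adverse events.

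An analysis plan can choose how to count days after the last contact, but it cannot recover data that nobody collected. Inpatients are scored daily to day 29, so the gap is confined to discharged patients. Discharge may itself depend on treatment, so the gap could differ between arms. The protocol gives nothing from which to estimate such a difference.

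**Working it through.** The protocol states no figure for the share of the day-29 period left unobserved, so there is none to reproduce. Its stated power of 83.15% belongs to the primary endpoint and does not bear on this point.

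**Inputs**
- Endpoint horizon: day 29 (synopsis, 6.2, 11.6.2).
- Margin: 7 days either side (Table 1), admissible under 8.5.1.
- Daily scoring while in hospital (11.6.1).

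**Step 1: earliest compliant final contact.** 29 − 7 = day 22.

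**Step 2: days left uncollected when the call comes at the earliest edge.** Uncollected days = 29 − max(22, discharge day).

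| Discharge day | Uncollected days | Share of 29 days |
|---|---|---|
| 22 or earlier | 29 − 22 = 7 | 24.1% |
| 25 | 29 − 25 = 4 | 13.8% |
| 28 | 29 − 28 = 1 | 3.4% |

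On 28 elapsed days the maximum is 7/28 = 25.0%. A contact on days 29 to 36 that asks back to day 29 leaves none.

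**Step 3: how often this could happen.** The protocol gives no distribution of call dates. The range for a patient discharged by day 22 runs from 0 days (call on or after day 29) to 7 days (call on day 22). As an illustration only, assume calls spread evenly over days 22 to 36:
- share before day 29: 7/14 = 50%
- mean shortfall: (7²/2)/14 = 1.75 days
- SD: √[(7³/3)/14 − 1.75²] = √(8.17 − 3.06) = 2.26 days

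With whole-day calls the figures are 7/15 = 47%, mean 28/15 = 1.87 and SD √(140/15 − 1.87²) = 2.42. Since the text names day 29 as the target, real calls may cluster more closely around it.

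**Step 4: effect on a count.** Take a hypothetical patient off oxygen from day 10 and called on day 22.
- Count cut at the call: 22 − 10 + 1 = 13 free days.
- Last status carried to day 29: 29 − 10 + 1 = 20 free days.
- If the patient stays well, the true count is 20: the first rule is 7 too low and the second is right.
- If the patient restarts oxygen on day 25 and stays on it, the true count is 24 − 10 + 1 = 15: the first rule is 2 too low and the second 5 too high.

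The protocol states neither rule and gives no rate of late relapse, so the error cannot be sized from it.

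**The case against.** The strongest reply is that the protocol means day 29. Sections 7.1.5, 8.5.3, 8.5.4 and 11.6.1 all say so, and section 7.1.6 puts the closing investigations of withdrawn patients on day 29 as well. In Table 1 the row for the WHO scale and NEWS is blank in the follow-up column that carries the margin. Several parts of this reply stand:

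- A reader might infer that day-29 WHO status is planned to be recorded up to a week early. Table 1 does not support that: WHO status after discharge is governed by 8.5.3 and 11.6.1, which give no margin.
- A reader might infer that a quarter of the window is lost across the endpoints in general. The documents do not support that either. The margin belongs to the follow-up column for arms 1-4, and the sub-studies have their own column without it. Inpatients are scored daily. Patients enter needing oxygen, so discharge is normally already an improvement and the primary endpoint is hardly touched. Deaths by day 29 can be recovered from the day-60 and day-90 checks.
- A reader might infer that day counts will be cut at the call date. No section says so, and how to count days after the last contact is commonly left to the analysis plan.
- The check-ups in 10.1 are a partial safeguard, but they cover only problems still ongoing. A patient who is well on day 22 and relapses on day 25 is not covered.

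What the reply does not remove is the conflict itself. Section 8.5.1 makes the earlier call compliant, the adverse-event row of Table 1 is marked for that same contact, and 8.5.4 makes the call the end of study. Section 8.5.3 also says clinical endpoints are obtained daily for all patients, yet for those discharged early it provides only two calls.

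**Conclusion.** The point holds as a conflict between one cell of Table 1 and the text, with a limited but real consequence. For main-study patients already discharged, a compliant final call on days 22 to 28 leaves 1 to 7 days uncollected for restart of oxygen or ventilation, readmission and serious adverse events. The maximum needs discharge by day 22 and a call on day 22.

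The endpoints affected are oxygenation-free and ventilator-free days, whose analyses are exploratory, and late safety reporting. No confirmatory conclusion depends on the window. The effect is probably modest, because most discharged patients are likely to be off oxygen, but the documents give no rate with which to confirm that. The even spread of call dates in the working is an assumption, not something the protocol states. The correction is still worth making, because data not collected cannot be restored later and the change is small.

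**What to change.** - In Table 1, replace the two-sided margin on the follow-up contact for arms 1-4 with a one-sided one: day 29, 0 to +7.
- Align sections 8.5.3, 8.5.4 and 11.6.1 with that window.
- State in 8.5.3 or 8.5.4 that the call records WHO category as of day 29, and any oxygen use, ventilation, readmission and serious adverse events up to day 29, with dates.
- Require any contact made before day 29 to be repeated on or after day 29.

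The cost is one table cell and a sentence or two. Some calls move a few days later, recall is slightly longer, and an occasional patient is called twice. No visits are added.
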